## TRIAL TREATMENT AND REGIMEN

The intervention will include the provision of an IPB on fire-related injuries, and facilitation to implement the briefing. Any Centre allocated to the control arm, ‘usual care’, will continue to use health promotion guidelines if they are already using them. A schematic diagram of the trial and the IPB is attached to this protocol.

There are 3 arms to this RCT:

I_1_ = Provision of IPB and facilitation for delivering it;

I_2_ = Provision of IPB without facilitation;

C =Usual care.

### Facilitation of the IPB and compliance with the intervention

A facilitation package will be designed to ensure as consistent an approach to facilitation within each intervention Children’s Centre as possible. Discussions will take place between each Fire & Rescue Service local to the four study coordinating centres about the IPB and its implementation. The package will comprise the following:

1. Training session run jointly between the local research team and the Fire & Rescue Service. This will be followed by a meeting run by the same team to design a plan for implementing the IPB in each Children’s Centre and Centres will be expected to provide at least one fire safety session for all parents taking part in the study.
2. One month follow-up telephone contact from the research team to monitor progress and answer any questions;
3. Three month face-to-face meeting between Children’s Centre and research team to monitor progress;
4. Additional meeting at 4-5 months if any Children’s Centre in a study coordinating centre is experiencing difficulties or problems in implementing the IPB;
5. Eight month follow-up telephone contact to monitor progress.

Each contact with a Children’s Centre will be recorded by each research team, together with relevant field notes, on a form and retained within the study notes in each study coordinating centre. Compliance with the intervention will be assessed from the telephone and face to face contacts.

Potential risks and burdens for research participants.

We do not anticipate any potential risks to study participants. The main burden for Children’s Centres will be the time taken to complete questionnaires, undertake the interview and the self-completion tools (see above for details). For family participants, the main obligation will be the time taken to complete the questionnaires (baseline and follow-up). For those families in the IPB with facilitation arm there will also be the time taken to attend between 1 - 5 fire safety sessions at the Children's Centre.

If any participants have suffered a house fire or has had relatives of friends injured in one this may cause distress when parents complete questionnaires. Researchers will be trained to respond sensitively in such situations for example when discussing the study with parents or helping them to complete questionnaires. Specific advice is given in the IPB for Children's Centres about undertaking fire safety sessions in such circumstances.

It is possible that during any home visits that researchers may be told or become aware of child protection issues. All researchers undertaking home visits will be trained in child protection and will follow local safeguarding procedures.

###

### Criteria for terminating trial

There are no adverse events anticipated and no interim analyses will be undertaken. The TSC will decide on the appropriateness of establishing a separate data monitoring and ethics committee (DMEC) should an adverse event occur.

**ANALYSES**

# Statistics

### Methods

An analysis plan will be produced by the trial statistician and health economist, who will oversee and/or undertake the statistical and economic analyses.

All analyses will be conducted on an intention-to-treat basis in that families and Children’s Centre managers and staff will be analysed in the group to which they were randomised, regardless of the intervention actually received (eg. if the family moved and used a different Children’s Centre). Analyses will conform to a pre-specified analysis plan and will be undertaken blind to treatment arm allocation.

Characteristics of Children’s Centres and families at baseline will be compared informally between the three treatment arms. The primary outcome measure (having a fire escape plan at 12 months) will be described using frequencies and percentages and compared between treatment arms (I_1_ vs C; I_2_ vs C and I_1_ vs I_2_) using random effects logistic regression to estimate odds ratios and 95% CI. This analysis will have families at level one and Children’s Centres at level two, to allow for clustering of responses within Children's Centres. The primary analysis will adjust for randomisation stratum (study coordinating centre) as a fixed effect and will also adjust for the lead agency of the Children's Centre (Local Authority or NHS led), having a fire escape plan at baseline and deprivation (measured using IMD2007 obtained from families’ postcode). Deprivation has been specified as it is strongly associated with house fire injuries^2,3^ and measures of deprivation have previously been found to be associated with the effectiveness of home injury prevention interventions^18^.

The ICC and 95% CI will be estimated for the primary outcome measure from the regression models. Models will be checked by examining level 2 residuals for normality and constant variance and level 1 and level 2 residuals for outliers.

Sub-group analyses will explore differential effects by deprivation, measured using the IMD2007, by adding interaction terms to the regression model for the primary outcome measure. IMD will be entered as a continuous covariate if there is a linear relationship with outcome.

The secondary binary outcome measures at family level will be described using frequencies and percentages and compared between treatment arms (I_1_ vs C; I_2_ vs C and I_1_ vs I_2_) using random effects logistic regression to estimate odds ratios and 95% CI, allowing for clustering of responses within Children's Centres. The analyses will adjust for randomisation stratum (study coordinating centre) as a fixed effect and will also adjust for the lead agency of the Children's Centre (Local Authority or NHS led), baseline value of the outcome measure and deprivation (measured using IMD2007 obtained from families’ postcode). The analysis of knowledge scores will be undertaken using random effects linear regression to estimate differences between treatment arms and 95% CI, allowing for clustering of responses within Children's Centres. A residuals analysis will be carried out to check the assumptions of the analysis, and if they are invalid transformations will be considered and if no suitable transformation can be found the score will be dichotomised and analysed using random effects logistic regression. Secondary outcome measures at the level of Children’s centre will be compared using logistic regression if binary and linear regression if continuous, adjusting for randomisation stratum (study coordinating centre) and lead agency of the Children's Centre (Local Authority or NHS led).

A complete case analysis will be undertaken. If any Children’s Centres are lost to follow-up we will consider a range of approaches to undertaking sensitivity analyses to assess the robustness of the findings.

No interim analyses will be undertaken.

Health economic analysis

To assess the cost-effectiveness of implementing an Injury Prevention Briefing in Children’s Centres for preventing fire-related injuries, firstly, resource-use data collected throughout the trial will be combined with unit cost information and summed to obtain an average cost per person (together with its uncertainty) for each intervention. Secondly, these cost data will be combined with the clinical effectiveness data (e.g. proportion of families who have a fire escape plan) to inform the incremental cost-effectiveness analysis. Sensitivity analysis will be undertaken to assess the robustness of the results to any assumptions made in the analysis.

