## PRIMARY OBJECTIVE

To test the hypothesis that providing facilitation for delivering the fire-related injury IPB to Children’s Centres is more effective, and cost-effective, than providing the fire-related IPB without facilitation or than usual care in increasing the proportion of families attending Children’s Centre who have a fire escape plan. The primary objective relates to fire escape planning as there was evidence from the systematic reviews and decision analyses described above that interventions can be effective and cost effective in increasing fire escape planning by families. Although the best evidence exists for interventions to promote smoke alarm use, this was not chosen as the primary outcome measure due to the high prevalence of functioning smoke alarms (> 90%) found in the interviews with parents attending Children’s Centres in an earlier piece of work within the programme.

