### Sample size and justification

11 Children’s Centres per arm will allow an absolute difference in the percentage of families with a fire escape plan of 20% in arm I_1_ or arm I_2_ compared to the control arm to be detected. This assumes a control arm prevalence of 42% (obtained from interviews with parents in Children’s Centres in earlier work in the programme of research), 80% power (2-sided 5% significance), an intraclass correlation coefficient of 0.05 (obtained from interviews with parents in Children’s Centres in earlier work in the programme of research) and that outcomes are assessed on 20 families per Children’s Centre. This gives a total of 33 Children’s Centres. In order that all study coordinating centres recruit the same number of Children’s Centres we will recruit a total of 36 Children’s Centres (9 per study coordinating centre), which will also allow for a potential drop-out of one centre per study arm. In order to achieve outcome data on 20 families per Children’s Centre we will aim to recruit 30 families per Children’s Centre; a total of 1080 families.

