### Assessment of efficacy

Unless stated otherwise, all comparisons will be made between I_1_ vs C; I_2_ vs C and I_1_ vs I_2_ arms.

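### Fitted in the usual way, the primary random effects logistic model on 36 centres runs at about 7.5–9% type I error per comparison, not the 5% used for sizing; a small-sample method should be named

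*Protocol*

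**What the plan says.** The Protocol's Methods section (under Statistics) compares the three arms pairwise on having a fire escape plan at 12 months, "using random effects logistic regression to estimate odds ratios and 95% CI". Families are level one and Children's Centres level two. The model adjusts for study coordinating centre (four strata, fixed effect), lead agency, baseline fire escape plan and IMD2007.

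The section on sample size and justification claims "80% power (2-sided 5% significance"). The effect sought is stated as "absolute difference in the percentage of families with a fire escape plan of 20% in arm I_1_ or arm I_2_ compared to the control arm". The section assumes a control prevalence of 42%, "an intraclass correlation coefficient of 0.05" and that "outcomes are assessed on 20 families per Children’s Centre". It arrives at 11 centres per arm (33 in all) and recruits 36.

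No section names an estimator, a reference distribution or a degrees-of-freedom method for the primary model. The detail is left to an analysis plan.

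**The concern.** A treatment effect in a cluster trial is judged against variation between centres, so the number of centres sets the precision with which that variation is known. Here 36 centres support an intercept, two arm terms, three stratum terms and lead agency. Maximum likelihood does not correct the between-centre variance for parameters already spent, and a Wald z interval treats the estimated variance as known. Both push the same way: standard errors too small and intervals too narrow.

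The sizing claims a 5% two-sided level. If the test runs nearer 9%, a borderline positive result carries almost twice the stated chance of error. It would then also feed the primary economic outcome, cost per family with a fire escape plan.

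**Working it through.** **1. The plan's own figure.** For 42% against 62%, 80% power, two-sided 5%:
- Uncorrected n per arm = [1.96·√(2·0.52·0.48) + 0.8416·√(0.42·0.58 + 0.62·0.38)]² / 0.20² = 96.8.
- With continuity correction: (96.8/4)·[1 + √(1 + 4/(96.8·0.20))]² = 106.5, so 107.
- Design effect: 1 + 19·0.05 = 1.95.
- Centres per arm: 107·1.95/20 = 10.43, so 11, or 33 in total.

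The stated 11 per arm reproduces. The calculation uses a normal critical value for one comparison.

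**2. Centre-level degrees of freedom.** Intercept 1 + arms 2 + strata 3 + lead agency 1 = 7, so 36 − 7 = 29. Baseline plan and IMD vary within centres and are not counted.

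**3. Analytic approximation.** Suppose maximum likelihood scales the centre-level variance by about 29/36. The true level of a nominal 5% z test is then 2·P(T₂₉ > 1.96·√(29/36)) = 2·P(T₂₉ > 1.759) = 8.9%. A normal reference alone, with a correct variance, would give 2·P(T₂₉ > 1.96) = 6.0%. Most of the excess therefore comes from the variance estimate.

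**4. Null simulation.** The model was fitted by maximum likelihood (15-point Gauss-Hermite quadrature) and tested with Wald z at 1.96, with 5,000 data sets per scenario and Monte Carlo error of about 0.4 points.
- From the Protocol: 12 centres per arm, four strata of nine centres, 20 families per centre, ICC 0.05, the listed covariates.
- Assumed: the estimator and test, 30% of centres NHS-led, the covariate effects, and the spread of centre sizes. An ICC of 0.05 on the proportion scale was set as a logit-scale variance of 0.227.

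| Scenario | Type I error per comparison |
|---|---|
| Base case | 8.9% |
| Stratum adjustment only | 8.2% |
| Unequal centre sizes, mean 20 | 9.0% |
| ICC 0.02 | 7.6% |
| ICC 0.10 | 8.9% |
| 33 centres | 9.2% |

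Two separately coded simulations of the same fit gave 8.7% and about 7.5–8%. Keeping the maximum likelihood standard error but using t on 29 df still gave 7.6% in the base case, so changing the critical value alone is not enough.

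**5. Small-sample alternative.** A centre-level two-stage analysis was run on 6,000 null data sets. It fits a logistic model without arm, then compares centre mean residuals between arms on about 29 df. It rejected 5.0%, 4.8% and 4.9% for the three pairs.

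**6. Power with a t reference.**
- 12 per arm: SE = √[(0.42·0.58 + 0.62·0.38)/(240/1.95)] = 0.0624. The noncentrality is 0.20/0.0624 = 3.21, and on 29 df power is 87%. Simulated power for the two-stage analysis was 86–87%.
- 11 per arm: SE = 0.0652, noncentrality 3.07, 33 − 7 = 26 df, power 84%.

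**The case against.** The strongest objection is that the Protocol does not state the thing criticised. It names a model class, not an estimator. Restricted pseudo-likelihood with Kenward-Roger degrees of freedom is itself a way to fit a random effects logistic regression, so the text already permits the remedy. The choice is also one that an analysis plan commonly makes. This stands in part. It rules out saying that the trial's test fails to hold 5%; one can say only that the usual fit would fail. The recommendation survives because the model, the 36 centres and the 5% level are all Protocol text, and the default way of joining them does not deliver that level.

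The lead-agency split, covariate effects and ICC after adjustment are also not in the documents. That is fair, and the result is therefore given as a range. No scenario tried came close to 5%.

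A reader might also infer that three unadjusted comparisons give roughly a one-in-five chance of a false primary claim, since the base-case simulation has 19.8% for any of three. The documents do not support that reading.
- The primary objective concerns facilitation being better "than providing the fire-related IPB without facilitation or than usual care", that is, I1 against I2 or against C. I2 against C is not part of it, although the section on assessment of efficacy opens "Unless stated otherwise, all comparisons will be made between" and lists all three pairs.
- The Protocol claims no family-wise control and sizes each intervention arm against control. Whether distinct arms need such control is debated.

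**Conclusion.** The point holds in conditional form. With maximum likelihood and Wald z, the primary analysis has a type I error of about 7.5–9% per comparison rather than 5%, and nominal 95% intervals cover about 91–92%. This rests on the assumed estimator and on covariate assumptions outside the Protocol; it was stable across ICCs of 0.02 to 0.10, unequal centre sizes and the loss of one centre per arm. The sample size is not in dispute.

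The absence of a multiplicity rule is not an error in this plan. Family-wise control is an optional trade-off with a real price.

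**What to change.** State in the analysis plan that the primary confidence interval and p-value come from a small-sample method. Two options:
- Restricted pseudo-likelihood with Kenward-Roger degrees of freedom. This gives the planned odds ratios directly. Its error rate was not simulated here and should be checked at 36 centres.
- A centre-level two-stage adjusted analysis on about 29 df, which simulated at about 5%. In the form simulated it compares residuals on the proportion scale, so the plan would have to say how the odds ratio is reported alongside it.

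The cost is wording and wider intervals. By the approximation in step 3 the widening is (2.045/1.96)·√(36/29) = 1.16, about 16%, which is the width needed for honest coverage. Power stays above the stated 80%: about 87% at 12 centres per arm and 84% at 11. No further centres, families or data are needed.

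If the team also wants family-wise control over the three pairs, a closed test (overall 2-df test at 5%, then each pair at 5%) would provide it. On the same t and F basis, I1 against C would then have about 84% power at 12 centres per arm, or 78% if I2 lies midway between I1 and C. At 11 per arm these become 80% and 73%. The team should make that choice knowing that power can fall below 80%.

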**Family participants**

Baseline and follow-up data will be collected by self-completion questionnaire. Baseline questionnaires will be given to family participants when they attend Children’s Centres by the researchers from each of the four study coordinating centres or by the relevant Children’s Centre staff, or will be posted by Children’s Centre staff. Questionnaires can be self-completed whilst at the Children’s Centre and handed to researchers or Children’s Centre staff, taken home and completed, or completed wherever the parents prefer and returned to researchers using freepost envelopes. One reminder will be sent to any parent who does not return the questionnaire. Follow-up data and the reminder, if necessary, will be collected by postal, telephone, home visit, or at Children’s Centres, which ever method is preferred by the participant. If necessary, a home visit will be undertaken to help completion of a questionnaire. Mode of administration will be recorded. Data will be entered onto identical databases at each study coordinating centre and stored on NHS or University servers. Once data collection is completed, data will be merged onto one database prior to analysis. At the end of the trial, data from all centres will be archived by the Nottingham centre for a period of seven years as set out in the University of Nottingham’s Code of Research Conduct.

The questionnaires are in the process of being developed and will be sent to the REC prior to being used within the study. Questionnaires will include questions on socio-demographic information about the household, previous fire-related accidents, fire safety behaviours and fire-safety equipment, knowledge and understanding of what causes fires, home safety information provided by Children’s Centres and their perception of the effectiveness of this information. The follow –up questionnaire will be identical to the baseline questionnaire except it will not collect socio-demographic data and it will collect data about resource-use and expenditure incurred as a result of the intervention; i.e. travel costs to attend educational sessions, equipment purchased and services attended. (e.g. smoking cessation). Parents returning completed questionnaires will be sent £5 gift vouchers for use in local stores as previous systematic reviews show small monetary incentives increase response rates^15^. Questionnaires will be developed and piloted with families between January – April 2011.

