### Secondary endpoints

1. The proportion of families with smoke alarms fitted and working on every level will be compared between treatment arms by estimating odds ratios and 95% CI;
2. The proportion of families who report fire-setting or match play by their children will be compared between treatment arms by estimating odds ratios and 95% CI;
3. The proportion of families who have a bedtime routine for preventing fires will be compared between treatment arms by estimating odds ratios and 95% CI;
4. The proportion of families who take part in smoking cessation courses/support will be compared between treatment arms by estimating odds ratios and 95% CI;
5. Scores of knowledge of the causes of fires in the home will be compared between treatment arms using random effects linear regression to estimate a mean difference in score plus 95%CI;
6. The proportion of families satisfied with the home safety information provided by Children’s Centre will be compared between treatment arms by estimating odds ratios and 95% CI;
7. Comparison of families’ resource-use and expenditure in the I_1_ and I_2_ arms incurred as a result of the intervention will be compared using incremental cost effectiveness ratios.

Children’s Centres as participants

1. The proportion of Children’s Centres providing information and advice on the prevention of fire-related injury including fire escape planning, smoke alarms, preventing fire setting or match play, use of bedtime routines for preventing fires, smoking cessation and referral to smoking cessation services. These will be compared between treatment arms by estimating OR and 95% CI.
2. The identification of barriers and facilitators to Children’s Centres implementing the IPB (only in Children’s Centres in the I_1_ and I_2_ arms) (qualitative data analysis);
3. Resource-use and expenditure incurred as a result of the intervention in the I_1_ and I_2_ arms will be compared using incremental cost effectiveness ratios;
4. The success of the process of implementing the IPB in Children’s Centres (using telephone and face-face contact during the intervention period (qualitative data analysis) and the implementation measurement tool that will be developed based on the PARIHS framework)^16^ (quantitative data which will be compared between treatment arms using OR and 95% CI for binary or ordinal data and linear regression for continuous data, if assumptions are met).

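### Read literally, the knowledge-score regression names only clustering and leaves out the baseline score and the randomisation stratum; one clause would settle the ambiguity and could improve precision

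*Protocol*

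**What the plan says.** The Methods text on secondary outcomes in the protocol's Statistics section runs in this order.

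1. Binary family outcomes are introduced: "The secondary binary outcome measures at family level will be described using frequencies and percentages". They are compared by random effects logistic regression, allowing for clustering.
2. Covariates follow: "The analyses will adjust for randomisation stratum (study coordinating centre) as a fixed effect and will also adjust for the lead agency". The same sentence adds "baseline value of the outcome measure and deprivation" (IMD2007).
3. The knowledge score gets its own model: "The analysis of knowledge scores will be undertaken using random effects linear regression to estimate differences between treatment arms and 95% CI, allowing for clustering". If assumptions fail and no transformation helps, the score is dichotomised and analysed by random effects logistic regression.
4. Centre-level outcomes get logistic or linear regression, with stratum and lead agency named again.

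The Statistical methods row of the Synopsis keeps the same order. The primary outcome, earlier in Methods, is adjusted for stratum, lead agency, baseline value and deprivation.

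The data needed for adjustment are collected. Under Data collection (Family participants), the questionnaires cover "knowledge and understanding of what causes fires", and the follow-up form "will be identical to the baseline questionnaire except it will not collect socio-demographic data" and adds resource-use items. Under Recruitment, a family counts as recruited only once it has completed the consent form and the baseline questionnaire. Under Randomisation and blinding, the stratum is the study coordinating centre (four strata), so it is known for every Centre.

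**The concern.** Each model in this paragraph seems to set out its own terms. The knowledge-score sentence repeats the allowance for clustering, which the binary sentence had already given, but not the covariates. The Centre-level sentence after it restates its covariates. An analyst who follows the text literally would adjust the primary, binary family-level and Centre-level outcomes for stratum and leave the knowledge score unadjusted.

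Precision is what would be lost. Without the baseline score, chance differences in baseline knowledge between about a dozen Centres per arm stay in the estimated mean difference. If scores differ by area, omitting the stratum leaves that variation in the error term, and the standard error is larger than the design warrants. Two statisticians could also build different models from this text, a choice best closed before data are seen.

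**Working it through.** **The plan's own figure.** Sample size and justification gives 42% against 62%, 80% power, two-sided 5%, ICC 0.05 and 20 families per Centre.

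- The continuity-corrected two-proportion formula gives 107 families per arm.
- Design effect: 1 + (20 − 1) × 0.05 = 1.95.
- 107 × 1.95 = 208.65 families; 208.65 / 20 = 10.43, rounded up to 11 Centres per arm.

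This reproduces the stated 11. It concerns the fire escape plan only. The protocol states no SD, ICC, effect size or power for the knowledge score.

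**Assumptions for the knowledge score.**

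- ICC 0.05, borrowed from the primary outcome.
- 20 families per Centre and 12 Centres per arm (36 recruited over three arms).
- Baseline to follow-up correlation r = 0.3, 0.5 or 0.7.
- Share s of between-Centre variance explained by stratum = 0, 0.25 or 0.5.
- Baseline explains the same share of variance between and within Centres.

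**Unadjusted precision, in SD units.**

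- SE of a difference between two arms = √(2 × 1.95 / 240) = 0.1275.
- Difference detectable with 80% power = (1.96 + 0.84) × 0.1275 = 0.357.
- With 11 Centres per arm the two figures are 0.133 and 0.373.

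**Adding the baseline score.** The SE is multiplied by √(1 − r²).

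| r | SE multiplier | Cut in SE | Detectable difference (12 Centres) |
|---|---|---|---|
| 0.3 | √0.91 = 0.954 | 4.6% | 0.341 SD |
| 0.5 | √0.75 = 0.866 | 13.4% | 0.309 SD |
| 0.7 | √0.51 = 0.714 | 28.6% | 0.255 SD |

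The percentage cuts do not depend on the number of Centres or on the borrowed ICC.

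**Adding the stratum alone.** The variance of a Centre mean is 0.05 × (1 − s) + 0.95 / 20, which is 0.0975 when s = 0.

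- s = 0.25: 0.0850 / 0.0975 = 0.872; √0.872 = 0.934, a cut of 6.6%.
- s = 0.5: 0.0725 / 0.0975 = 0.744; √0.744 = 0.862, a cut of 13.8%.
- s = 0: no gain.

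**Both together.** With r = 0.5 and s = 0.25 the variance ratio is 0.75 × 0.872 = 0.654; √0.654 = 0.809, a cut of about 19%.

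Lead agency and deprivation are also absent on the literal reading. Their contribution is not quantified here.

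**The case against.** The strongest reply is that the protocol is silent and does not exclude adjustment. Nothing in it says the knowledge-score model is unadjusted. The adjustment sentence stands directly before the knowledge-score sentence, has the analyses in general as its subject, and does not itself contain the word binary. It may be meant to cover all family-level secondary outcomes, with the next sentence only changing logistic to linear regression. The fallback supports this: once dichotomised, the score is a binary family outcome and the list would plainly apply. The literal reading would therefore adjust the fallback but not the main analysis. This stands, and for that reason the point is one of ambiguous wording.

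A reader might take item 5 of Secondary endpoints (Assessment of efficacy), "Scores of knowledge of the causes of fires in the home will be compared between treatment arms using random effects linear regression", as confirming an unadjusted model. It does not. That section names no covariates for any outcome, including those that Methods clearly adjusts.

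A reader might also infer that this is the only continuous family outcome. The Secondary endpoint list also includes families' resource use and expenditure, although that goes to the economic analysis.

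Finally, covariates for a secondary outcome are often left to the analysis plan, which Methods says will be produced. That carries less weight here, because this protocol already fixes covariates for the neighbouring outcomes and states the knowledge model beside them without any.

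**Conclusion.** The point holds as an ambiguity with an easy gain in precision. On the literal reading of Methods and the Synopsis, the knowledge score is analysed without its baseline value or the randomisation stratum, both of which are available. The documents do not show that this is intended.

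If the model were unadjusted, the randomised comparison would still be unbiased, and only precision on one secondary outcome would suffer. Adjusting for baseline would cut the standard error by about 5% to 29% for assumed correlations of 0.3 to 0.7. Stratum alone would cut it by 0 to 14% if it explains none to half of the between-Centre variance, given the borrowed ICC. These figures are illustrative: the protocol supplies neither quantity, and with no correlation and no area differences there would be no gain. They should not be read as a demonstrated loss of power. The sample size and primary analysis are unaffected. This is a desirable clarification of low severity.

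**What to change.** In Methods, and in the Statistical methods row of the Synopsis, add one clause to the knowledge-score sentence. It should say that the regression, and its dichotomised fallback, adjust for baseline knowledge score, randomisation stratum (fixed effect), lead agency and IMD2007, as for the other family-level outcomes. Item 5 of Secondary endpoints needs no change.

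The cost is a line of wording, with no new data and no change to sample size. Under the planned complete case analysis, a family that left the baseline knowledge items blank would drop out of the adjusted model. The same already applies to the other family outcomes that are adjusted for baseline.
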